## Abstract

**Background:**

The standard care in patients with a painful osteoporotic vertebral compression fracture (VCF) is conservative therapy. Percutaneous vertebroplasty (PV), a minimally invasive technique, is a new treatment option. Recent randomized controlled trials (RCT) provide conflicting results: two sham-controlled studies showed no benefit of PV while an unmasked but controlled RCT (VERTOS II) found effective pain relief at acceptable costs. The objective of this study is to compare pain relief after PV with a sham intervention in selected patients with an acute osteoporotic VCF using the same strict inclusion criteria as in VERTOS II. Secondary outcome measures are back pain related disability and quality of life.

**Methods:**

The VERTOS IV study is a prospective, multicenter RCT with pain relief as primary endpoint. Patients with a painful osteoporotic VCF with bone edema on MR imaging, local back pain for 6 weeks or less, osteopenia and aged 50 years or older, after obtaining informed consent, are included and randomized for PV or a sham intervention. In total 180 patients will be enrolled. Follow-up is at regular intervals during a 1-year period with a standard Visual Analogue Scale (VAS) score for pain and pain medication. Necessary additional therapies and complications are recorded.

**Discussion:**

The VERTOS IV study is a methodologically sound RCT designed to assess pain relief after PV compared to a sham intervention in patients with an acute osteoporotic VCF selected on strict inclusion criteria.

**Trial registration:**

This study is registered at ClinicalTrials.gov., NCT01200277.

## Background

Because of an aging population, osteoporosis and associated fractures are becoming an important health issue, especially in Western societies. The incidence of a new vertebral compression fracture (VCF) in Europe is, at age 50-79 years, 1% per year in women and 0.6% per year in men and at age 75-79 years the incidence is 2.9% per year in women and 1.4% per year in men [1]. VCFs are associated with an increased incidence of mortality and morbidity, including back pain, loss of height, kyphotic deformity and a reduction in quality of life [2].

Conservative therapy, bed rest, pain medication, physiotherapy and bracing, is considered the standard care in patients with symptomatic osteoporotic VCFs. Since the introduction of percutaneous vertebroplasty (PV), this minimal invasive therapy that involves injection of bone cement in the fractured vertebral body, has gained popularity to stabilize osteoporotic VCFs with resultant relief of associated local back pain. PV is considered an accepted pain therapy in many centres and acknowledged as a useful additional option in the care for patients with osteoporotic VCFs.

In 1984 PV was developed in France for the treatment of painful aggressive vertebral angioma [3]. In the following years the indications for PV were expanded to vertebral fractures caused by osteoporosis, trauma, malignant or benign vertebral tumors and vertebral osteonecrosis. Presently, PV is most frequently performed to treat patients with painful osteoporotic VCFs.

Many prospective and retrospective studies on PV have been published and described a high clinical success rate [4-12]. A recent systematic literature review demonstrated the effectiveness of PV in 87% of patients in terms of pain relief as well as a short- and long-term improvement of physical function [13]. However, these studies did not have a control group. In fact, the natural course of pain in similar patients with a VCF was unknown. Two non-randomised controlled trials have been published comparing PV with conservative therapy [14,15]. Both studies demonstrated a significant better improvement in pain scores after PV on the short-term. However, after 6 months no differences could be demonstrated. VERTOS, the first randomised controlled trial (RCT) with a limited group of 34 patients, reported only on short-term results [16]. Longer term results could not be obtained due to the cross-over of many patients from optimal pain medication to PV. VERTOS confirmed immediate pain relief and improvement of mobility, function and stature after PV. The short-term results after PV were significantly better compared to pain medication in these patients with sub-acute or chronic osteoporotic VCFs.

Recently, three RCTs concerning PV have been published with conflicting results. Investigators in two randomized controlled trials [17,18] concluded that there is no benefit to PV over a sham placebo procedure involving the injection of local anesthetic into the area adjacent to the fracture. In the study by Buchbinder et al [17], 78 patients with one or two painful osteoporotic VCFs were randomized to receive either PV or a sham procedure, which included infiltration of anesthetic into the pedicular periosteum. The primary measured outcome was overall pain at 3 months. Despite significant reductions in overall pain in both groups, there was no significant advantage of PV over the sham procedure. In the study by Kallmes et al [18], 131 patients with one to three painful osteoporotic VCFs were randomized to undergo either PV or a simulated sham procedure, which included infiltration of anesthetic into the periosteum of the posterior lamina. The primary outcomes were scores on the modified Roland-Morris Disability Questionnaire (RDQ) and average pain intensity during the preceding 24 hours at 1 month. Treatment group crossover was permitted at 1 month. At 1 month, there was no significant difference between the two groups in either the RDQ score or the pain rating. In the third RCT, VERTOS II [19], PV was compared to optimal conservative treatment in 202 patients who were 50 years or older, had vertebral compression fractures on spine radiograph, had experienced back pain for 6 weeks or less, and a visual analogue scale (VAS) score for pain of 5 or more. The primary outcome was pain relief at 1 month and 1 year as measured by VAS score. The authors concluded that in a subgroup of patients with acute osteoporotic vertebral compression fractures and persistent pain, percutaneous PV is effective and safe. Pain relief after PV is immediate, is sustained for at least a year, and is significantly greater than that achieved with conservative treatment, at an acceptable cost.

The most important differences between the two sham studies and VERTOS II is patient selection. In the sham studies both acute and chronic fractures were included while in VERTOS II only acute fractures were eligible. In addition, bone edema in the affected vertebra was not a consistent inclusion criterion in the sham studies. The sham studies lacked a control group without intervention. The discordant results from the sham studies, on the one hand, and VERTOS II, on the other hand, have incited much debate [20-24]. Apparently clinicians do still not know how to best treat their patients. The objectives of this study is to evaluate the efficacy of bone cement injection in PV for patients with acute painful osteoporotic compression fractures, as compared with a simulated placebo procedure without injection of bone cement. We hypothesize that patients who had undergone PV would report less pain at 1 day, 1 week and 1, 3, 6 and 12 months (the primary outcomes) than those in the sham control group. In addition, we hypothesize that the back pain related disability is less and the quality of life (QOL) is better of patients undergoing PV compared with patients in the simulated placebo condition

## Methods

### Study design

VERTOS IV is a multicenter RCT concerning the treatment of patients with a painful osteoporotic VCF. Patients are recruited on the Radiology departments of the participating hospitals and randomized to PV or a simulated procedure. Upon obtaining informed consent an independent central telephone operator completes the randomisation procedure, using a computer program. The maximum allowed unbalance (block size) is six, with a maximum sample size of 84 for each participating centre. A total of 180 patients will be enrolled, 90 in each group. This is based on the assumption of a 1.5 point difference in pain relief (VAS Score) and a 20% withdrawal rate (α = 0.05 and β = 0.20, 7 measurement points). The enrolment of patients will take place in four centres in The Netherlands: St. Elisabeth Ziekenhuis in Tilburg, Catharina Ziekenhuis in Eindhoven, Medisch Spectrum Twente in Enschede and Albert Schweitzer Ziekenhuis in Dordrecht. Randomization will start January 2011 with an expected completion of enrolment by January 2013. There is a one-year follow-up, with the possibility of an extended follow-up at two years.

The overall Institutional Review Board approval is obtained at the St. Elisabeth Hospital in Tilburg (NL33978.008.10). In addition, each participating centre will obtain a local Institutional Review Board Approval. This study is registered at ClinicalTrials.gov., NCT01200277.

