### Sample size considerations

Conform Kallmes et al. [18], we expect a 1.5 point difference in pain relief as measured by VAS score. Given that there are seven measurement points (α = 0.05 and β = 0.20) we need 142 patients in total). Assuming a withdrawal rate of 20%, a total of 180 patients will be enrolled, 90 in each group. We used G-Power to calculate the sample size.

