### Statistical analysis

The data will be analysed according to the intention-to-treat principle. Standard statistical techniques will be used to describe characteristics of patients in both groups. We will compare baseline characteristics in the two treatment groups and if incomparability appears, we will in secondary analysis, adjust for differences. The primary outcome, significant pain relief, will be compared between groups using analysis of variance for repeated measures. If adjustment for possible baseline incomparability is needed, analysis of covariance will be done. Since we expect that the difference between the two groups will become evident from 3 months onwards, the analysis will also be performed only using scores before and 3, 6, and 12 months after the procedure.

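### Allocation appears to be blocked within centre, but the stated covariate rule would not bring centre into the primary ANOVA; adding it is a small, nearly free improvement

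*Protocol article*

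**What the plan says.** **Allocation (Study design).** "The enrolment of patients will take place in four centres in The Netherlands", and the randomisation rule reads: "The maximum allowed unbalance (block size) is six, with a maximum sample size of 84 for each participating centre". The block size and the per-centre cap stand in one sentence. The article does not say that randomisation is stratified by centre.

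**Analysis (Statistical analysis).** "The primary outcome, significant pain relief, will be compared between groups using analysis of variance for repeated measures". The only route by which another variable enters is conditional: "If adjustment for possible baseline incomparability is needed, analysis of covariance will be done". The same section places adjustment for baseline differences in a secondary analysis. Centre is not mentioned, either as included or as excluded.

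**Sample size (Sample size considerations).** The target is a 1.5-point VAS difference between the arms, and the evaluable number follows from it: "Given that there are seven measurement points (α = 0.05 and β = 0.20) we need 142 patients in total". Enrolment is then raised to 180 (90 per arm) to allow for one patient in five withdrawing. No standard deviation, within-patient correlation or between-centre variance is given.

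**The concern.** When allocation is balanced within a factor that affects the outcome, that factor's variation no longer contributes to the difference between the arms. A model that omits the factor still counts the variation as error. The reported standard error is then larger than the true one, the confidence interval is too wide and the p-value too large.

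The stated covariate rule makes this more than an unmentioned detail. It admits a variable only when the arms differ on it at baseline. A factor balanced by the randomisation blocks will essentially never differ, so followed literally the rule keeps out the one factor the design controls.

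Centre differences are plausible here. Recruitment runs through each hospital's radiology department, scanners may be 1, 1.5 or 3 Tesla, needles are of two gauges, and the sham cues are delivered by the operator. At stake is how faithfully the reported interval reflects the design, in a trial presented as settling conflicting earlier results.

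**Working it through.** **Step 1: is allocation blocked within centre?** 84 / 6 = 14 exactly. A per-centre cap that is a whole number of blocks, stated together with the block size, points to one blocked list per centre. This is an inference. The wording also merges two quantities: a permuted block of six with 1:1 allocation allows an imbalance of at most three, so a block size of six and a maximum imbalance of six are not the same rule.

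**Step 2: the plan's own figure.** 142 / (1 − 0.20) = 177.5, rounded up to 178; the stated 180 agrees. The 142 itself cannot be rebuilt without a standard deviation and correlation. For a single-time comparison (1.5 points, 71 per arm, two-sided 0.05 assumed, 80% power) the implied standard deviation is 3.19. It cancels from the ratios below.

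**Step 3: effect of omitting centre.** Let ICC be centre's share of the variance of the quantity tested. The article gives no value, so 0.02, 0.05 and 0.10 are assumptions. With balance within centre:

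- reported SE / true SE: r = 1/√(1 − ICC)
- actual size without centre: 2[1 − Φ(1.96 r)]
- power without centre: Φ((2.80 − 1.96) r)
- power with centre: Φ(2.80 r − 1.96)

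Here 2.80 = 1.96 + 0.84, the value giving 80% power when ICC is 0. Unrounded normal quantiles were used for the table.

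| ICC | SE overstated | Size without centre | Power without | Power with | Forgone |
|---|---|---|---|---|---|
| 0.02 | 1.0% | 0.048 | 80.24% | 80.79% | 0.5 points (0.548 unrounded) |
| 0.05 | 2.6% | 0.044 | 80.61% | 81.97% | 1.4 points |
| 0.10 | 5.4% | 0.039 | 81.25% | 83.97% | 2.7 points |

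Power without centre already exceeds 80%, because balance has reduced the true variance. The gain from adding centre must be measured from that column, not from a flat 80%.

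**Step 4: simulation of a single outcome.** Four centres, permuted blocks of six, 142 patients, 10,000 runs, ICC 0.10. Without centre, the mean reported SE was 0.527 against a true SE of 0.511, and the size was 0.043. With centre, the mean reported SE was 0.507 and the size 0.052. The direction agrees and the effect is a little smaller than the formula gives. When blocks were not within centre, the unadjusted size was 0.051, so there was no conservatism.

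**Step 5: simulation of repeated measures.** Seven time points, assumed within-patient correlation 0.5, blocks of six within four centres.

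- Group main effect without centre: size about 0.040 at ICC 0.05 and 0.038 at ICC 0.10. With centre in the model it returned to about 0.05.
- Change from baseline, constant centre effect: size 0.048 and 0.051, so not conservative, because the centre effect cancels within each patient.
- Change from baseline, centres also differing in change over time: size about 0.042.

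**The case against.** **Silence in a condensed article is not a decision.** A reader might infer that the plan has chosen to leave centre out. It does not say so, and a fuller protocol or analysis plan may include it. That stands as far as it goes. But the article does name a primary model and a rule for admitting covariates, and that rule would not admit centre. The point rests on the stated rule.

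**Stratification is not stated.** This also stands. Without blocking within centre the conservatism disappears, so the point is conditional on it.

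**The planned test may not be the one affected.** The repeated measures include the pre-procedure score and the outcome is pain relief, so the treatment test may well be group-by-time. A constant centre effect then cancels, and a centre main effect alone changes nothing. The article does not say which test is primary. The objection limits the point to the between-group effect, or to centres that differ in their course over time.

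**The effect is small and on the safe side.** Correct: every ICC is assumed, and up to 0.05 the power forgone is 1.4 points at most.

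**Conclusion.** The point holds as a minor improvement. Given allocation blocked within centre and centre differences in outcome, the stated model reports a standard error for the between-group effect that is too large by about 1.0%, 2.6% or 5.4% at an assumed ICC of 0.02, 0.05 or 0.10, and forgoes about 0.5, 1.4 or 2.7 points of power. If centres do not differ, nothing is lost.

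Three stronger conclusions might be drawn, and the documents support none of them:

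- **That the precision gained by the design is lost.** Balance within centre still lowers the true variance of the treatment difference; the reported standard error merely fails to show it.
- **That the trial's validity is at risk.** The error is conservative and type I error is not inflated.
- **That power rises from 80% to about 81%, 82% or 84%.** The unadjusted test already has about 80.2%, 80.6% or 81.3%, so the gain is smaller.

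**What to change.** State whether randomisation is stratified by centre, and whether six is the block size or the largest permitted imbalance. If it is stratified, prespecify centre (four levels, fixed effect) in the primary VAS model and in the Qualeffo and Roland-Morris models, independently of the baseline comparison. Say which term is the primary treatment test; if it is group-by-time, add centre-by-time as well, since the centre main effect does nothing for that test.

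The cost is a sentence or two in the analysis section and three degrees of freedom for the centre term, out of about 140 (142 evaluable patients less two group means). A centre-by-time term uses further degrees of freedom in the within-patient part of the model. Sample size and conduct are unaffected.

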### Interventions

The pre-procedural work-up consists of: ECG, chest X-ray and blood sampling. One hour prior to the procedure 2 g cefazolin is administered intravenously as prophylaxis. Patients are brought to the angio suite, where sterile preparation for surgery is performed. Using fluoroscopic guidance, the practitioner infiltrates the skin and subcutaneous tissues overlying the pedicle of the target vertebra or vertebrae with 1% lidocaine and infiltrates the periosteum of the pedicles with 0.25% bupivacaine (marcaine). Patients are then randomly assigned to undergo either the full PV procedure or the sham intervention. For the PV procedure, 11-gauge or 13-gauge needles are passed into the central aspect of the target vertebra or vertebrae. Bone cement is prepared on the bench and injected under constant fluoroscopy into the vertebral body. Injection is stopped when the cement reaches to the posterior aspect of the vertebral body or leaks into an extraosseous space, such as the intervertebral disk or an epidural or paravertebral vein. During the sham intervention, verbal and physical cues, such as pressure on the patient's back, are given, and the methacrylate monomer is opened to simulate the odor associated with mixing of bone cement, but the needle is not placed and cement is not injected. After the procedure, all patients are monitored in the supine position for 1 to 2 hours before discharge. Cross-over will not be offered before 6 months after randomization.

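### The allocation rule gives six as both maximum imbalance and block size, which cannot be one scheme; how far allocations can be foreseen depends on which is meant

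*Protocol article*

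**What the plan says.** The Study design section of the protocol article describes the allocation rule in one sentence: "The maximum allowed unbalance (block size) is six, with a maximum sample size of 84 for each participating centre". The same section says that "an independent central telephone operator completes the randomisation procedure, using a computer program", that "The enrolment of patients will take place in four centres in The Netherlands", and that "A total of 180 patients will be enrolled, 90 in each group". It also says that "Patients are recruited on the Radiology departments of the participating hospitals".

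The Interventions section places random assignment in the angio suite, after the local anaesthetic has been infiltrated. In the sham arm verbal and physical cues are given, "but the needle is not placed and cement is not injected".

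The article does not say whether the block size is constant, or whether each centre has its own list.

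**The concern.** The sentence treats block size and maximum imbalance as one quantity. They are two, and with equal allocation they take different values. A reader cannot tell which scheme the randomisation program runs.

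This is more than wording, because the possible schemes differ in how far a centre can foresee the next allocation. The practitioner cannot be masked to whether a needle is placed and cement injected, and so knows the past allocations that he or she carried out. Recruitment runs through radiology departments, and some eligibility criteria in the Patients section call for judgement, such as focal tenderness or the severity of a cardio-pulmonary condition. If the next allocation can be foreseen, it may influence who is approached, accepted or scheduled next. Masking the patient does not correct that.

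**Working it through.** **Inputs.** Six, given as both block size and maximum imbalance; a cap of 84 per centre; four centres; 180 patients at 1:1 (all from Study design). If centres recruit equally, each has 180/4 = 45 patients. The practitioner's knowledge of the arm is inferred from the description of the sham in Interventions.

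**Step 1: is six the maximum imbalance of a block of six?** A 1:1 block of six has C(6,3) = 20 orderings. The largest running difference occurs when the first three patients all go to one arm: 3 − 0 = 3. So the stated six is not reproduced. In general the maximum is half the block size, so an imbalance of 6 needs a block of 12. Nor is six the trial-wide maximum for separate lists in four centres, which would be 4 × 3 = 12.

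**Step 2: predictability if six is a block size in one visible list.** An allocation is certain once one arm has used its three places. The best guess is the arm with more places left.

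| Position in block | Certain | Best guess correct |
|---|---|---|
| 1 | 0 | 0.50 |
| 2 | 0 | 3/5 = 0.60 |
| 3 | 0 | 0.6 × 1/2 + 0.4 × 3/4 = 0.60 |
| 4 | 0.10 | 0.1 × 1 + 0.9 × 2/3 = 0.70 |
| 5 | 0.40 | 0.4 × 1 + 0.6 × 1/2 = 0.70 |
| 6 | 1.00 | 1.00 |
| Sum | 1.5 | 4.1 |

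Certain: 1.5/6 = 25%. Guessed correctly: 4.1/6 = 68.3%, against 50% by chance. With every block filled, 25% of 180 is 45 patients. With 45 per centre, each list holds seven full blocks and half a block, and the half block adds no certain allocation: 4 × 7 × 1.5 = 42. The 25% is therefore an upper figure.

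**Step 3: the other readings.**

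| Reading | Certain | Guessed correctly |
|---|---|---|
| Blocks of six, one visible list per centre | 25% | 68.3% |
| Blocks of twelve, one visible list per centre | 14.3% | 64.3% |
| Imbalance limit 6 (big-stick rule), 45 in a centre | 6.2% | 53.1% |
| Same, 84 in a centre | 7.1% | 53.5% |
| Same, one list of 180 | 7.7% | 53.9% |
| Blocks of six over all four centres, each seeing only its own patients | not computed | 51.5% |

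The big-stick rule tosses a fair coin unless the limit is reached and then forces the lagging arm, so the guess rate is 50% plus half the certain share: 50 + 6.2/2 = 53.1%. The last row is a simulation assuming equal recruitment. It rises to 54.8% if a centre also knew where each block began.

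**Step 4: would hidden, varying block sizes help?** Guessing the lagging arm needs no knowledge of block size, because the arms are level at the end of every block. Expected correct guesses per block are 1.5 (size 2), 2.83 (size 4), 4.1 (size 6) and 5.33 (size 8). With sizes mixed equally:

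- 4 and 6: (2.83 + 4.1)/10 = 69.3%
- 4, 6 and 8: (2.83 + 4.1 + 5.33)/18 = 68.1%
- 2, 4 and 6: (1.5 + 2.83 + 4.1)/12 = 70.3%

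The guess rate stays near 68–70%. What hidden sizes mainly take away is certainty about particular allocations.

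**The case against.** The strongest reply is that the predictability figures rest on premises the article does not contain. It does not say that the block size is constant or that lists are per centre. The cap of 84 is a multiple of six, but that is only suggestive. A sentence that contradicts itself also gives no licence to take its most predictable reading as fact. All of this stands, so the figures must be given as a range, with 25% and 68% as the top.

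A second reply is that the route to bias is narrow. Allocation is central and by telephone. The Patients section puts consent before MRI, densitometry, blood screening and the internist's consultation, and the Interventions section puts assignment after infiltration. A forecast has to remain correct through that chain while others are being enrolled. Bone edema is defined by signal on named sequences in the MRI protocol section, and every patient contacted is registered. The article does not say that those who recruit also perform the procedures. These points reduce the risk considerably. They do not remove it: a central list hides future entries but not the arms already delivered, and registration may reveal selective enrolment without preventing it.

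A third reply is that a journal article leaves stratification and block variation to the full protocol. That is correct, and their absence is not the point here. The point is a rule that the article does state, and states inconsistently.

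A reader might infer that centres knew a fixed block of six and could work out a quarter of the allocations, or that selection bias occurred or was likely. The documents support neither inference. A reader might also suppose that the 68% guess rate comes from a constant, published block size; Step 4 shows that it does not.

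**Conclusion.** The inconsistency holds without conditions: a 1:1 block of six has a maximum imbalance of 3, so six cannot be both quantities. A block of six would stay within a limit of six, but that limit would never act, and it is not what equating the two terms says.

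The consequence for concealment is conditional. It ranges from a guess rate of about 51–54% (blocks across centres, or an imbalance limit of 6) to 68%, with up to 25% of allocations certain, for constant blocks of six per centre. The upper end assumes a known block size, one list per centre, and someone with a say in enrolment who sees every past allocation there. The point deserves correction because the protocol's own Background names patient selection as the main difference between the conflicting earlier trials, and because the remedy is cheap. It does not touch the sample size: 142/0.80 = 177.5, rounded up to 178, is consistent with the planned 180.

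**What to change.** 1. Rewrite the sentence so that block size and maximum imbalance are separate quantities with their own values, and say whether lists are kept per centre.
2. Preferably use an imbalance-limited scheme within centre (big-stick or biased-coin) with a stated limit. For the big-stick rule, a limit of 6 gives about 6–8% certain and 53–54% guessable; a limit of 3, the same maximum as a block of six, gives about 15–16% and 58%. Both improve on 25% and 68%.
3. If permuted blocks are kept, vary their sizes at random, hold the sizes only at the randomisation office, and leave them out of documents that centres see. This mainly removes the certain allocations and leaves the guess rate near 68–70%.

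The cost is a setting in the randomisation program and a one-sentence correction. With a limit above 3, the possible imbalance per centre is slightly larger than with blocks of six. The planned 180 patients do not change.
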